Ledalab version v.3.2.9, a MATLAB-based computer program, is used to extract EDA using a continuous decomposition analysis (CDA) method [81]. Epoched EDA data are then preprocessed individually using visual analysis and subsequent data grooming to reduce noise, which includes manual smoothing using a 5-second Hann window [82,83] and a filter of a unidirectional first-order Butterworth low-pass filter with a similar cutoff frequency of 5 Hz [83,84]. The traced EDA artifacts are then corrected using a spline interpolation within a 5-second pre/post parameter [85]. The CDA method uses parameters based on the previous works of Benedek and Kaernbach [81], which optimizes the EDA data and applies a 0.2-Hz Gaussian smoothing window within a 10-second grid size to detect significant peaks of >0.05 µS [86]. For the resting baseline and recovery conditions, SCL is extracted by using the *CDA.Tonic* parameter, which computes for the mean tonic EDA within the epoched response window (150-second block), in an aggregated 10-second moving within-window averaging method. In the case of processing the EDA stimulation condition data, a similar CDA method is used (Bateman functions comprising onset, amplitude, 1 and 2 parameters). The software can identify significant peaks of >0.05 µS [87], within a response window of 1 to 4 seconds poststimulus [82,88] across the stimulation condition block that consisted of 10 trials. To represent the sympathetic activity in the form of EDA, *CDA.SCR* was identified [82,87], which was then averaged across trials (0 responses not included) within the stimulation block condition as estimate of mean sympathetic activity, reflecting the individual’s amplitude of responsiveness to sensory stimulus. To remove the impact of within and between-subject variance, analysis was performed using z-transformed individual *CDA.SCR* scores [82]. Furthermore, to correct for skewed distribution of skin conductance data scores and to meet assumptions required for parametric statistical analyses, normalization of SCL and SCR data for each intersection was performed using square root transformation [83,89-91]. This logarithmic transformation is determined as follows: *√(CDA.Tonic)* and *√(CDA.SCR+1)*.

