#### Statistical Data

Descriptive statistics involving measures of central tendencies, variation, and dispersion are used to describe the salient characteristics of the data gathered. Demographic data related to participant gender, age, BMI, type of school (ie, public, private), number of parents working, primary caregiver, highest educational attainment of caregiver, family income, and parent’s occupation will be gathered and considered in further statistical analyses. The Shapiro-Wilk test of normal is used to determine normality at baseline of the characteristics of the participants included in the study. Univariate and multivariate tests are likewise used to determine whether there are group and subgroup baseline similarities at critical alpha=.05. Variables deemed as non-normally distributed or significantly different at baseline are used as covariates. General linear modeling is used to determine whether effects of ethnicity or environment (used as the independent variables [IV] in this study) can explain differences in the behavioral measures of the participants at a critical value of alpha=.05. Autonomic regulation is represented in this research as HF (n.u.) and LF (n.u.) of HRV and mean EDA (SCL/SCR) values as multivariates. Multivariate analysis of variance (MANOVA) tests will be used to determine whether effects of ethnicity or environment (used as IV in this study) can explain differences in the multivariate set of DVs, across the different research aims, with the different pairwise combinations in between 3 events (resting baseline, stimulation, and recovery). Effect size is interpreted using the values of Cohen *d*. Statistical analysis will be computed using SPSS version 23.0.

Specific to this report, sample size and power analysis are performed using G*Power version 3.1.9.2 [91,92]. Post hoc analysis of computed achieved power of the pilot data will be ascertained to determine the needed effect size for a subsequent a priori computation of required sample size for MANOVA tests.

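### The z-transformation of the stimulation skin-conductance response is meant to remove between-subject variance, which is what the group MANOVA tests; its reference is not named, and a within-child z would strip the outcome of amplitude

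*Protocol article*

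**What the plan says.** The article's Neurophysiological Data section (under Data Analysis) defines the EDA outcome for the stimulation condition in four steps.

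1. Peaks above 0.05 µS are identified in a window after each tone "across the stimulation condition block that consisted of 10 trials".
2. The SCR measure is taken from these, "which was then averaged across trials (0 responses not included) within the stimulation block condition as estimate of mean sympathetic activity", and is described as "reflecting the individual’s amplitude of responsiveness to sensory stimulus".
3. The scores are standardised: "To remove the impact of within and between-subject variance, analysis was performed using z-transformed individual" SCR scores. The mean and SD used for the z score are not stated.
4. A further sentence, opened by *Furthermore*, says that "normalization of SCL and SCR data for each intersection was performed using square root transformation". The printed formulas are √(CDA.Tonic) for the skin conductance level (SCL) and √(CDA.SCR+1) for SCR. The text calls this transformation logarithmic.

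The Statistical Data section then says: "Autonomic regulation is represented in this research as HF (n.u.) and LF (n.u.) of HRV and mean EDA (SCL/SCR) values as multivariates". The MANOVA is to show whether ethnicity or environment "can explain differences in the multivariate set of DVs, across the different research aims".

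**The concern.** Each child belongs to one ethnic and environmental group, so any group effect on SCR is part of the variance between children. A step intended to remove that variance works against the hypotheses the variable is meant to test. The description of SCR as the individual's amplitude of response makes the child's own level the quantity of interest, and a within-child z score deletes that level.

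Two things raise the stakes. The Introduction and the Neurophysiological Measures section bring in EDA because LF is contested as a sympathetic measure. Stimulation is also the only one of the three conditions in which a stimulus is presented. If the third response variable carries no amplitude information there, a finding of no EDA difference, or of a difference, could come from the scoring alone. The pilot analysis used resting SCL only and could not have revealed this.

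**Working it through.** **The plan's own figure.** The article gives no figure for the z step. Table 2 shows where SCR enters the design, as one of 3 response variables. With 4 groups, f²(V) = 0.0625 and N = 88, the Pillai global test has λ = 3 × 88 × 0.0625 = 16.5, df 3 × 3 = 9 and 3 × (88 − 4 + 3 − 3) = 252, and power 0.8094. This matches Table 2. Nothing in it depends on how SCR is scored.

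**Three references for z.** Let a child have r responding trials out of 10, with mean amplitude m and SD s over those trials.

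*(a) Within child, responding trials only.* The child's mean z is Σ(x − m)/(r·s) = 0 for every child, whatever the amplitude. The outcome is constant and no group test exists. This is exact.

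*(b) Within child over all 10 trials, then averaged over non-zero trials.* The mean over all trials is rm/10, and the sum of squares about it is (r − 1)s² + r·m²(1 − r/10). Dividing by 9 for the variance and writing c = s/m, the child's score is

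(1 − r/10) / √{[(r − 1)c² + r(1 − r/10)]/9}.

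The amplitude m has cancelled. What remains is the number of responses and the relative spread. Take trial amplitudes as log-normal with log-SD 0.6 (an assumption), so c² = e^0.36 − 1 = 0.433:

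- r = 5: 0.5/√[(4 × 0.433 + 2.5)/9] = 0.73
- r = 7: 0.3/√[(6 × 0.433 + 2.1)/9] = 0.42
- r = 9: 0.1/√[(8 × 0.433 + 0.9)/9] = 0.14
- r = 10: 0

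The score falls as the child responds to more tones.

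*(c) Across the whole sample.* z is a linear function of the child's mean with one common constant and scale. MANOVA statistics do not change under such a rescaling. The group test is the same as on raw means, and no between-subject variance is removed.

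**Simulation.** Assumptions: 600 runs, 32 children per group, 10 trials, log-normal amplitudes, between-child log-SD 0.5, trial log-SD 0.6, 25% zero trials in both groups, true shift of 0.8 between-child SD, two-sided t test on SCR alone at 0.05. The sample size and effect size of 0.8 follow the Participants section; the rest is assumed.

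| SCR score | Difference detected |
|---|---|
| Raw child mean | 75% |
| √(raw mean + 1) | 77% |
| z across whole sample | 75% |
| z within child, all 10 trials, non-zero averaged | 5% |
| z within child, responding trials | no test possible |

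A second simulation (2,000 runs, child and trial SD both 0.6, 70% response rate, 0.05 µS threshold) gave 6% at 22 and 8% at 32 per group for reading (b). Log child means gave 66% and 83% there.

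With zero trials set at 35% in one group and 15% in the other, and no amplitude difference, reading (b) rejected in 100% of runs of the first simulation. Raw means rejected in 5%.

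**The square root.** Raw SCR amplitudes are not negative, so CDA.SCR + 1 is at least 1 and the printed root is always defined. If the root were instead taken on z scores, values below −1 would have none. That is 15.9% of values if z is normal (0.159 × 32 ≈ 5 children per group, 0.159 × 128 ≈ 20 overall). In the first simulation it was about 9% of children for a whole-sample z and about 11% of trials for a within-child z; in the second, about 6% and 10–12%. In the first simulation, dropping those children under a whole-sample z lowered detection from 75% to 66%.

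**The case against.** The strongest reply follows the order of the sentences. SCR is averaged over trials first, which leaves one number per child, and only then z-transformed. One number cannot be standardised within a child, so the z would have to be taken across children, and that does no harm. This stands as a possible reading, and the word *individual* does not settle the matter, since it may describe only the scores. But the sample-wide reading makes the stated purpose false, because such a z removes no between-subject variance. The text is either harmful or wrong about what it does.

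A reader might infer that the stimulation EDA outcome cannot show any group difference. The documents do not support that. It is untrue for a whole-sample z, and under reading (b) the score can differ strongly between groups, though through the number of zero responses. A reader might also infer that the planned square root is undefined for some children. The printed formula is on CDA.SCR, and the same sentence applies the root to SCL, which is never z-scored. *Furthermore* leaves the order open, so the undefined values arise only if the root follows the z step.

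The scope is limited, as the defence would say: one of three response variables in one of three conditions. The article calls EDA supplementary and adjunct, and no reported pilot result or sample size depends on the z step. A constant outcome under reading (a) would also be noticed at analysis. Reading (b) would not announce itself in that way.

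A condensed article may leave the z reference to a fuller protocol. It does, however, state the purpose of the step, and that purpose is what conflicts with the test.

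**Conclusion.** The concern holds in a limited form. The stated aim of the z step, removing between-subject variance, contradicts the use of mean SCR as an outcome for between-subject factors. The damage depends on an unnamed reference. A within-child z makes the outcome constant, or leaves it insensitive to amplitude (5% to 8% detection in the simulations) while open to differences in the number of zero responses. A whole-sample z leaves the group test intact. The zero mean under (a), the cancellation of amplitude under (b) and the invariance under (c) are algebra. The detection rates and the shares below −1 rest on assumed distributions and should be read as illustrations. Resting and recovery SCL and the HRV variables are unaffected.

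**What to change.** - Drop the z step from the between-group analysis. If a z is kept at all, state its reference mean and SD and do not standardise within child.
- Analyse each child's mean raw SCR amplitude with one named variance-stabilising transform, for example the printed √(SCR+1), and state that it acts on raw values.
- Correct the description of the square root as logarithmic.
- Keep within-child z scores, if wanted, only to describe the pattern over the 10 tones.

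The cost is a few sentences in the EDA processing text and a rescore of the stimulation data. No new data are needed. If the intended z was sample-wide, dropping it loses nothing.

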#### Statistical Data

Descriptive statistics involving measures of central tendencies, variation, and dispersion are used to describe the salient characteristics of the data gathered. Demographic data related to participant gender, age, BMI, type of school (ie, public, private), number of parents working, primary caregiver, highest educational attainment of caregiver, family income, and parent’s occupation will be gathered and considered in further statistical analyses. The Shapiro-Wilk test of normal is used to determine normality at baseline of the characteristics of the participants included in the study. Univariate and multivariate tests are likewise used to determine whether there are group and subgroup baseline similarities at critical alpha=.05. Variables deemed as non-normally distributed or significantly different at baseline are used as covariates. General linear modeling is used to determine whether effects of ethnicity or environment (used as the independent variables [IV] in this study) can explain differences in the behavioral measures of the participants at a critical value of alpha=.05. Autonomic regulation is represented in this research as HF (n.u.) and LF (n.u.) of HRV and mean EDA (SCL/SCR) values as multivariates. Multivariate analysis of variance (MANOVA) tests will be used to determine whether effects of ethnicity or environment (used as IV in this study) can explain differences in the multivariate set of DVs, across the different research aims, with the different pairwise combinations in between 3 events (resting baseline, stimulation, and recovery). Effect size is interpreted using the values of Cohen *d*. Statistical analysis will be computed using SPSS version 23.0.

Specific to this report, sample size and power analysis are performed using G*Power version 3.1.9.2 [91,92]. Post hoc analysis of computed achieved power of the pilot data will be ascertained to determine the needed effect size for a subsequent a priori computation of required sample size for MANOVA tests.

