### Research Aims

Considering the available evidence in the current literature and our perceived gaps in the knowledge related to our topic, in this study, we study the role of ethnicity and environment in the regulation of response to sensory stimuli among children from a neurophysiological perspective by applying the theory of allostasis. We aim to explore differences in the regulation of response to sensory stimuli in children through their ethnicity (as proxy measure of genetic influence) and environments (as a general measure of beliefs, practices, behaviors, culture, parenting practices, physical landscapes, and sociocultural and economic aspects). Specific to this manuscript, the authors also aim to determine the ample sample size needed for the main study, based on the pilot data presented.

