To measure resilience, the Child and Youth Resilience Measure (CYRM) [72], which was established through a process of interviews with youth and adults in countries around the world, was completed by the participants’ parents. Previous research has suggested that ethnicity and environmental experiences influence the development of resilient behaviors [73,74] and that it is likely moderated by autonomic activity [75-77]. We included resilience as a behavioral outcome measure to determine whether group differences in autonomic activity across conditions can be explained by our main dependent variables (DVs, ie, ethnicity, environment), or other factors, for which we may try to control. This research uses the 28-item (>10 years of age) or the 26-item (5-9 years of age) Person-Most-Knowledgeable questionnaire version, which was developed and validated by Ungar and Liebenberg [78]. The similar items between the 2 versions will be used for analysis. Although CYRM is originally in English, a translated Chinese version was recommended and provided by the authors and was used among Chinese participants in this research (personal communication, [name], 2015).

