### Group Differences: MANOVA

Preliminary data from 30 gender-controlled and age-matched participants with a mean age of 8.667 (SD 1.759) are analyzed for the influence of physical environments on the neurophysiological regulation of response to sensory stimuli using the HF (n.u.) and LF (n.u.) bands of HRV and EDA-SCL during the resting baseline condition as DVs. On the basis of the Shapiro-Wilk test and independent samples *t* test, BMI was normally distributed (*P*=.149) and similar at baseline (*P*=.57) between urban- and rural-dwelling participants.

The mean HF (n.u.) for the resting baseline condition was computed at 62.301 (SD 15.903) for urban-dwelling children, which is higher than the rural-dwelling group (mean 52.096, SD 15.125). This is the other way around for the LF (n.u.), where the rural-dwelling group (mean 29.228, SD 10.639) fared better than the urban-dwelling group (mean 24.171, SD 9.370). EDA-SCL showed almost similar values, with the urban group having slightly higher values (mean 1.929, SD 0.600) compared with their rural group (mean 1.900, SD 0.363).

**Table 1 table1:** Summary of demographics and statistical results.

Demographics		Urban (N=15)	Rural (N=15)	Total (N=30)	Shapiro-Wilk test	*t* test	*F* test			
							Pillai *V*	*F*	*P*	*d*

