**Output**		
	Noncentrality parameter *λ*	16.5000
	Critical *F*	1.9171
	Numerator df	9.0000
	Denominator df	252.0000
	Total sample size	88
	Actual power	0.8094
	Pillai *V*	0.1765

^a^Computation was based on *F* tests–MANOVA: Global effects with analysis of a priori to compute for the required sample size.

^b^This is the critical value.

^c^This is the specific formula to compute for the power.

Using physical environment (urban or rural setting) as IV and the values at resting conditions of the LF (n.u.), HF (n.u.), and SCL as DV, a multivariate analysis of covariance (MANCOVA) test, specifically Pillai *V*, was performed using BMI as a covariate. In the series of analyses of variance (ANOVAs) performed, results of the multivariate tests confirm that the differences in the measures of autonomic regulation considered as DV among the 2 sampled ethnic groups in this study are not significant using a critical alpha of .05 (*V*=0.107, *F*_3,26_=1.033, *P*=.39, *d*=0.692). A univariate analysis of individual DVs reveals similar nonsignificant differences between LF (n.u.) (*F*_1,30_=1.909, *P*=.18, *d*=.523), HF (n.u.) (*F*_1,30_=3.243, *P*=.08, *d*=0.681), and SCL (*F*_1,30_=0.025, *P*=.87, *d*=0.063) of the sampled groups. It remains unclear whether the sample size in our pilot findings confounded the influence of the physical environment of the participants in explaining differences in the autonomic regulation of response to sensory stimuli.. Thus, a subsequent power analysis of the sample reported is performed.

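### Covariates are chosen by a normality test or a baseline significance test, which detects confounding poorly and can adjust away part of the environment effect

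*Protocol article*

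**What the plan says.** Statistical Data lists the background variables to be collected: "Demographic data related to participant gender, age, BMI, type of school (ie, public, private), number of parents working, primary caregiver", followed by caregiver education, family income and parental occupation, nine in all. Two screens follow. The first is for distribution: "The Shapiro-Wilk test of normal is used to determine normality at baseline of the characteristics of the participants included in the study". The second is for group difference: "Univariate and multivariate tests are likewise used to determine whether there are group and subgroup baseline similarities at critical alpha=.05". The selection rule is then "Variables deemed as non-normally distributed or significantly different at baseline are used as covariates". No covariate is fixed in advance on subject-matter grounds.

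Three other places bear on this:

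- Research Aims describes the exposure as "environments (as a general measure of beliefs, practices, behaviors, culture, parenting practices, physical landscapes, and sociocultural and economic aspects". It treats ethnicity as a proxy for genetic influence.
- The Discussion treats socioeconomic measures as confounders, to be handled by stratification of the sample and by statistical means. It names neither the strata nor the adjustment set.
- In the pilot (Group Differences: MANOVA), "BMI was normally distributed" (P=.149) and was similar between groups (P=.57). The text after Table 2 nevertheless says that the multivariate test "was performed using BMI as a covariate".

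**The concern.** The four groups are not randomised, so adjustment is a main protection against confounding. Whether a variable confounds depends on its relation to both group and outcome. The rule looks at neither the outcome relation nor the causal role.

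- **Normality arm.** Linear models make assumptions about the residuals of the outcomes, not about the distribution of covariates. A skewed but balanced and irrelevant variable would be selected. Several of the listed variables are categorical, and for those a Shapiro-Wilk test has no meaning.
- **Significance arm.** With 22 or 32 per group, a moderate real imbalance will often give P>.05 and go unadjusted.
- **Exposure.** If income or education differs between urban and rural children, the rule adjusts for it, although Research Aims counts economic aspects as environment. Whether a comparison estimates the total effect of environment, or only the part not running through socioeconomic position, would then depend on a P value and could change from one comparison to the next.

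**Working it through.** **1. The plan's own figures.** Table 2 reproduces. With 4 groups, 3 responses, s=3 and f²=0.0625, N=88 gives df1 = 3×3 = 9, df2 = 3×(88−4−3+3) = 252, λ = 0.0625×88×3 = 16.5 and power 0.8094, as printed. The two group sizes in the article are therefore 22 (Table 2) and 32 (Participants). The pilot BMI test also reproduces: the pooled variance is (3.722² + 2.683²)/2 = 10.526, so t² = 0.678²/(10.526×2/15) = 0.328 and P=.572.

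**2. How often the .05 screen flags a real imbalance.** This is a two-sample t test, taken as two-sided because sidedness is not stated. It has df = 2n−2 and noncentrality δ√(n/2). The imbalances δ are assumptions.

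| True imbalance δ | n=22 per group | n=32 per group |
|---|---|---|
| 0.3 SD | 16% | 22% |
| 0.4 SD | 25% | 35% |
| 0.5 SD | 37% | 50% |

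At 0.5 SD the imbalance is missed 63% or 50% of the time. Conversely, if all nine variables were balanced and independent, the group test alone would select at least one with probability 1 − 0.95⁹ = 37%.

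**3. What a missed confounder costs.** In a simulation with no true group effect, one confounder imbalanced by 0.3 or 0.5 SD and a confounder-outcome correlation of 0.3 to 0.7 (all assumed), the rule left a mean bias of about 0.04 to 0.14 SD. Always adjusting left about 0. Type I error under the rule was about 0.04 to 0.07.

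**4. The normality arm.** A balanced, moderately skewed variable (log-normal, log-SD 0.5, assumed) was selected in 90% of simulated samples at n=22 and 96% at n=32.

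**5. Adjusting away the exposure.** Suppose the total environment effect is 0.8 SD and part of it runs through a socioeconomic variable (differences and paths assumed). The effect left after adjustment is 0.8 − (group difference × path):

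- 0.8 − 0.8×0.5 = 0.4
- 0.8 − 1.0×0.5 = 0.3
- 0.8 − 1.0×0.3 = 0.5

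In simulation the rule selected such a variable in 75 to 91% of samples at n=22 and 89 to 98% at n=32. The mean estimate fell from 0.8 to between 0.30 and 0.51.

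**6. Was BMI in the pilot model?** With N=30, two groups and three responses, the multivariate error df is 26 without a covariate and 25 with one. The article reports 3,26. With two groups, F = [V/(1−V)]×df2/3. Taking V=0.107 as rounded (0.1065 to 0.1075), 26 df gives 1.033 to 1.044, which includes the reported 1.033. With 25 df the largest value is 1.004.

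The univariate F values also equal squared unadjusted t statistics from Table 1:

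- HF: 10.205²/[(15.903² + 15.125²)/2 × 2/15] = 3.243 (reported 3.243)
- LF: 5.057²/[(9.370² + 10.639²)/2 × 2/15] = 1.909 (reported 1.909)
- SCL: 0.029²/[(0.600² + 0.363²)/2 × 2/15] = 0.026 (reported 0.025, within rounding of the means)

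**7. Power cost of a fixed set.** Each covariate takes 3 from df2. At N=88, three covariates give df2=243 and power 0.809, and nine give df2=225 and power 0.808. At N=128 power is 0.949 with none or three, and 0.948 with nine. No credit is taken for outcome variance that the covariates explain.

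**The case against.** The fairest defence has four parts, and much of it stands.

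- **Scale.** The study calls itself exploratory and the article is condensed. The imbalance sizes above are assumptions. In the pilot, age is identical by matching and BMI differs by only 0.678/3.244 = 0.21 SD. Bias from one missed confounder is modest, so it would be too strong to say that the covariate set decides the answer. The rule is nonetheless stated, not left open, and its normality arm has no justification at any sample size.
- **Socioeconomic variables are not always part of the exposure.** A reader might infer that they belong outside all four primary models. The documents do not support that. Research Aims places them under environment, so in a comparison of ethnicities within one environment they are potential confounders. The over-adjustment argument applies only where environment is the exposure. For the same reason, the adjustment sets may legitimately differ between contrasts, provided they are fixed in advance.
- **The pilot.** A reader might infer that BMI was used in place of school type, which the rule demanded. The first half is not shown, since the reported statistics match a model without BMI. The rule also does not say that only selected variables may be used. On school type, 12 of 15 urban children in public school would leave 3 in private, and 3+15 = 18 does not match the printed private total of 17. That part of Table 1 may be damaged, so no exact P value should rest on it.
- **Behavioural scores.** A reader might infer that the rule sweeps in temperament and resilience. The screening sentences concern participant characteristics, and Statistical Data treats behavioural measures as outcomes. The remark on resilience, "or other factors, for which we may try to control", is a separate and discretionary statement.

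**Conclusion.** The concern holds in this form. The selection rule is unsound in both arms: non-normality is irrelevant to confounding, and the .05 screen flags an assumed 0.3 to 0.5 SD imbalance in 16 to 37% of cases at 22 per group and 22 to 50% at 32. For the environment contrasts the rule can also remove part of the effect under study. How much depends on assumed paths, but the overlap between exposure and candidate covariates is in the documents themselves. The pilot adds a narrower point: BMI met neither criterion, is named as covariate, and does not appear in the reported F statistics, so the pilot account must be reconciled. It does not show that BMI displaced another covariate. The change should be made before the main analysis. It needs no larger sample.

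**What to change.** 1. Delete the selection sentence, and remove both screening tests as criteria for adjustment. Baseline characteristics can still be described.
2. Prespecify age and sex as covariates in every comparison, whatever the baseline tests show. Add BMI if the sponsor judges that it is not itself a consequence of environment.
3. Check normality on the residuals of the autonomic outcomes only.
4. For each contrast, state in advance whether the socioeconomic variables are confounders (the ethnicity contrast) or part of the exposure (the environment contrasts). Report the environment contrasts with socioeconomic adjustment only as a labelled sensitivity analysis. The contrast in which ethnicity and geographic environment both differ needs its own statement.
5. Reconcile the pilot text: either report the model that includes BMI with its own degrees of freedom, or describe the printed results as unadjusted.

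The cost is wording, a few degrees of freedom and one extra model. All the variables are already planned for collection, and power at N=88 stays at 0.809 with three covariates.
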